#### Secondary Analysis

A secondary analysis will aim to establish the cumulative impact of the components of the intervention (eg, remote monitoring and self-management training) on outcomes and assess “digital retention” and sustained digital device usage in visual and time-sensitive analyses using an N-of-1 design (see Table 3). N-of-1 designs use a patient as their own control and can assess the impact of incremental changes with respect to the intervention with frequent and repeated measurements of the outcome variable of interest (ie, pain over time) and are particularly applicable to digital health and mobile phone-based clinical trials [133]. An N-of-1 design allows for association of causality to interventions in real time and direct methods to estimate individual treatment effects and variation per patient. Using the funnel approach, an individual patient is observed repeatedly to graphically demonstrate the variation in pain and HRQL over time [134].

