#### Chronic Postsurgical Pain and Related Consequences

CaVS surgeries affect pain-sensitive structures as they invade muscle and visceral tissues, and involve the harvesting and manipulation of vessels. Such surgical tissue insults lead to pathological nervous system changes, collectively known as sensitization [16]—a function of neuronal modifiability [17]. Sensitization increases pain sensitivity (ie, hyperalgesia), augments the normal duration (ie, hyperpathia) and amplitude of pain, and results in abnormal interpretation of nonpainful stimuli as painful (ie, allodynia) [16]. In all cases, CPSP is, in part, a function of unrelieved acute postoperative (postop) pain that involves a transition phase [18] by virtue of these pathological mechanisms. In our review of 26 studies (n=2033; mean age 65.1 years) across 15 countries, CPSP prevalence following CaVS [11,12,18-41] ranged from 17-56%. The 2013 Canadian prospective Cardiac (CARD) pain study (n=1010) [11] reported more modestly varying CPSP prevalence rates of 40%, 22%, and 17% at 3, 6, and 12 months following surgery, respectively; pain was most commonly located along the sternal incision and saphenous vein harvesting sites. But other studies have reported 1-year CPSP prevalence rates as high as 39% [39] and 45% [40]. Rates of CPSP following vascular surgery are similar in range (25%), with moderate to severe pain typically presenting along the femoropopliteal bypass tunnel [42].

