##### Follow-Up

The SVN will collect outcome data for intervention and control groups following random allocation through discharge. Once in the community, patients in both groups will record their BPI-SF pain scores daily for 8 weeks using the tablet-based solutions. Data on 30-day event rates (ie, major postop complications) and hospital readmissions for both groups will be collected by a blinded RA via telephone interview at 30 days postoperation. At 3, 6, 9, and 12 months, additional telephone interviews conducted by the RA will assess (1) functional status, (2) depressive symptoms, (3) CPSP, and (4) patient-level cost of recovery (ie, AHCR).

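### The N-of-1 secondary analysis cannot support causal or individual treatment-effect claims, because components are delivered in one fixed, overlapping order while patients recover

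*Protocol article*

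**What the plan says.** The Secondary Analysis section states its purpose as follows: "A secondary analysis will aim to establish the cumulative impact of the components of the intervention". Remote monitoring and self-management training are given as examples, and outcomes are the target. The comparator is the same patient: "N-of-1 designs use a patient as their own control and can assess the impact of incremental changes with respect to the intervention". The inferential claim is: "An N-of-1 design allows for association of causality to interventions in real time". The same sentence goes on to claim that treatment effects can be estimated for each patient. The method is described as visual and time-sensitive, and as one in which "an individual patient is observed repeatedly to graphically demonstrate the variation in pain and HRQL over time". The randomized control arm is not mentioned.

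The delivery schedule is in the Stage 1 and Stage 2 text and in Table 2. The Follow-Up section adds that, once in the community, "patients in both groups will record their BPI-SF pain scores daily for 8 weeks using the tablet-based solutions".

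**The concern.** A patient can serve as own control for a causal claim when treatment periods are randomized, or are repeatedly switched on and off in a reasonably stable condition. Neither holds here. Components are added once each, in the same order for everyone, during weeks in which pain is expected to change anyway. Time since surgery and exposure to the components move together.

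A report that followed this section could present a falling pain curve as evidence that a component worked, or that it worked in a particular patient, when the same curve could arise from recovery alone. Statements about which parts of the program matter, and for whom, would then lack support.

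**Working it through.** **1. What the schedule allows**

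| Component | Start and duration | Source |
|---|---|---|
| Ward monitoring | Ward day 1, at transfer | Table 2, Stage 1 |
| Pain education video | Ward day 2; once seen, it cannot be withdrawn | Education; Table 2 |
| Home monitoring and daily check-ins | First 30 days after discharge | Table 2, Stage 2 |
| Restore | Seven weekly modules from the week of discharge | Self-Management Training; Table 2 |

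- Randomization takes place at transfer to the ward (Randomization and Allocation), when the first component is set up. No intervention-free phase is planned as a baseline. The abstract gives ward day 2 as the start, which would leave one ward day at most.
- Daily self-recorded pain scores begin in the community, after ward monitoring and education have been given. Before that, the study nurse collects outcome data until discharge, at a frequency the article does not state.
- Home monitoring and Restore both begin around discharge and overlap. On an assumed schedule (discharge on day 6, home monitoring for 30 days, Restore for 49 days), no day has home monitoring without Restore.
- The one planned withdrawal is the monitoring equipment, at about 30 days (Table 2; Feasibility). It happens once and at a fixed time, so it too is confounded with recovery. Any days left after the last Restore module come at the end of the series and have the same problem.

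**2. Size of the artefact when the true effect is zero**

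The article states no figure for this analysis, so there is nothing to reproduce. The decline below is an assumption.

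Let pain on day t be 60·exp(−kt), reaching 20 or 30 at day 56:

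- k = ln(60/20)/56 = 0.0196
- k = ln(60/30)/56 = 0.0124

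Apparent benefit = mean of the days before a component starts − mean of the days from its start onward. For a day-7 start with 14-day windows, only 7 earlier days exist.

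| Decline | Start day | 7-day windows | 14-day windows |
|---|---|---|---|
| 60 to 20 | 7 | 7.3 | 10.4 |
| 60 to 20 | 14 | 6.3 | 12.7 |
| 60 to 20 | 28 | 4.8 | 9.7 |
| 60 to 30 | 7 | 4.8 | 7.0 |
| 60 to 30 | 14 | 4.4 | 8.8 |
| 60 to 30 | 28 | 3.7 | 7.4 |

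Example (60 to 20, day 7, 7-day windows): 56.6 − 49.4 = 7.3 from unrounded means.

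The range is 3.7 to 7.3 points with 7-day windows and 7.0 to 12.7 with 14-day windows. Two of the 12 scenarios reach 10 points; both use 14-day windows and the steeper decline.

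**3. What a concurrent control does**

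Take a linear decline of D points over 56 days, with the contrast placed at discharge on day 6 (days 1-6 against days 7-56). The mean days are 3.5 and 31.5, so the apparent benefit is D × 28/55 = 0.51D. That is 5.1 points for D = 10 and 10.2 for D = 20. In a simulation with no effect (within-patient SD 10, autocorrelation 0.5, both assumed), declines of 0 to 40 points were tried in linear and exponential form. Subtracting the same contrast in a concurrent control left between −0.4 and 0.2 points in every case.

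**The case against.** The section names no estimator, and the before/after contrast above is one reading of it. The words on visual and time-sensitive analysis could cover a trend term, and an article may leave such detail to an analysis plan. The sentence on causality describes N-of-1 designs in general. Exposure may also vary from day to day, since Uptake of Technology plans daily use metrics. The analysis carries no stated test or decision.

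Part of this stands. The size of the artefact depends on choices the article does not make, and the stakes are limited to a secondary analysis. The core is untouched. The stated aim is to establish component impact with the patient as own control. With no intervention-free phase, a trend term would rest on an assumed shape of recovery. Day-to-day use is not randomized and may itself follow recovery. Aiming at cumulative impact does not help either, because a cumulative own-control change is equally mixed with recovery.

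Three stronger readings are tempting and should not be drawn:

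- **That recovery alone would generally reach the trial's 10-point minimally important difference.** Only 2 of 12 assumed scenarios do, and the 10 points in Sample Size is a between-group difference, not a within-patient threshold.
- **That an inert component would look beneficial in nearly every patient.** With within-patient SD 10 and autocorrelation 0.5 (assumed), the chance of any drop is 68-82% with 7-day windows and 84-98% with 14-day windows.
- **That the article documents natural recovery in untreated patients.** It cites "CPSP prevalence rates of 40%, 22%, and 17% at 3, 6, and 12 months following surgery, respectively" from a prospective cohort and does not call those patients untreated. These are prevalences, not intensities, and they fall after the 8-week diary. The same section also cites 1-year rates of 39% and 45%. The citation suggests a direction of change, not its size in the analysis window.

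**Conclusion.** The concern holds as a fault in what this secondary analysis claims. The own-control comparison cannot identify component effects or individual treatment effects under the delivery schedule that the article describes. This follows from the schedule and needs no numerical assumption.

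The amount of bias does need one. Under the assumed exponential decline it is about 4 to 7 points with 7-day windows and about 7 to 13 with 14-day windows; a flatter recovery would give less and a steeper one more. The randomized intention-to-treat comparison of the primary outcome is not affected. The change should be made, but the trial's main conclusion does not depend on it.

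**What to change.** - For any effect claim, compare the daily BPI-SF series of the two randomized arms over the same periods, for example with arm-by-time segments. Days since surgery are the cleaner scale, because discharge comes after randomization; postdischarge periods can also be shown.
- Interpret each segment as the effect of the whole package in that period. The comparison removes recovery shared by both arms but does not separate overlapping components.
- Keep individual trajectories, digital retention and device-use plots, labelled as descriptive.
- Delete the wording on causality and on individual treatment effects.

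**Cost:** revised wording and a modest extra analysis. No new data are needed, because both arms already keep the daily diary for 8 weeks. The price is that component-level and individual causal claims are given up.

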#### Subgroup Analyses

Two types of separate subgroup analyses are planned to determine the impact of gender-based pain expectations and patient sex on intervention effectiveness (see Table 3):

1. Patients will be stratified into high versus low GREP scores. The primary analyses examining the effect of the intervention on the worst score for the BPI-SF numeric rating scale *upon movement* (previous 24 hours) will be conducted. An interaction term for GREP score (low versus high) and the group allocation will be incorporated into the analyses to determine if gender-based pain expectations are associated with differences in the effect of the intervention on the primary outcome. If a significant interaction is identified, the primary analysis in these two groups will be performed.

2. Similarly, interaction between the intervention and patient sex will be examined.

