##### Sample Size

Assuming a two-sided type I error (alpha) of .05 and a standard deviation of 20 points in BPI-SF numeric rating scale scores (range 0-100), a total of 128 participants (ie, 64 individuals in each group) are required to provide 80% power to detect a minimally important difference of 10 points. This difference represents a moderate effect size (Cohen’s d=0.50) [126]. Assuming a 10% loss to follow-up, 144 total patients (or 72 per group) is required. We will use this sample size for each site, to allow for site-specific analyses with equal and sufficient power. If there is sufficient homogeneity between the Canadian and UK samples, the combined sample (eg, 256 patients with complete data) would provide 80% power to detect a difference in pain intensity scores of 8.6 points (Cohen’s d=0.43), assuming a generous design effect [127] of 1.5 due to the clustering of participants within the site.

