### Data Analyses

#### Primary Analyses

Table 3 summarizes all data analyses. Using the intent-to-treat principle [128], all patients will be included in the final analysis and according to the group to which they were randomly allocated. Descriptive statistics will be used to describe sample characteristics using measures of central tendency and dispersion for continuous factors, and frequencies and proportions for categorical factors. A two-sided significance level of .05 will be used for all inferential analyses. Statistical methods used will depend on the type and distribution of data for the outcome variable under study. If outcome data meet requirements for parametric statistics, a linear mixed model [129] will be used to assess the effects of the intervention on the primary outcome. An a priori contrast of the weekly average worst score for the BPI-SF numeric rating scale *upon movement* (previous 24 hours) will be used to evaluate the primary endpoint of acute postop pain at 30 days postrandomization.

Linear mixed models, using an autoregressive [130] covariance structure—allowing for correlations between measurements to decline as they are further apart in time—will be used to evaluate within-patient variation in patient-reported outcomes over 12 months of follow-up. Linear mixed models are a flexible and powerful approach to the analysis of data with a complex variance structure, such as correlated data [129-131]. Unlike traditional repeated-measures designs, these models do not require complete data on each patient and have increased statistical power [132]. Nonlinear mixed models will be used in the following cases: (1) if continuous data violate assumptions of normality [132] and (2) for categorical secondary outcomes (eg, adverse event). Chi-square tests of association will be used to assess the association between categorical secondary outcomes identified in the administrative data and intervention. Given that the data is derived from an RCT, complex modeling for these outcomes will not be performed, as potential confounders are considered to be adjusted for in the design. Finally, we will examine patterns of missing data and determine demographic and/or clinical characteristics that are related to missing data at each time point, and the potential impact on the primary findings.

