**Subgroup outcomes**				
	All outcomes	Effect will differ by gender (male versus female)	Worst postop pain intensity *upon movement* score in the past 24 hours measured by BPI-SF numeric rating scale	Interaction test
	All outcomes	Effect will differ by GREP^c^ scores (low versus high)	Worst postop pain intensity *upon movement* score in the past 24 hours measured by BPI-SF numeric rating scale	Interaction test

^a^BPI-SF: Brief Pain Inventory-Short Form.

^b^CPSP: chronic postsurgical pain.

^c^GREP: Gender Role Expectations of Pain.

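### The GREP interaction test uses a high/low split of a scored baseline measure, which gives away power in a test that is already weak; the continuous score should carry the test

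*Protocol article*

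**What the plan says.** Two subgroup questions are planned, one on gender-based pain expectations and one on patient sex. For the first, the Subgroup Analyses section of the protocol article states "Patients will be stratified into high versus low GREP scores" and then "An interaction term for GREP score (low versus high) and the group allocation will be incorporated into the analyses". Separate analyses in the high and low groups follow only if that interaction is significant. The subgroup block of Table 3 repeats the two-category form, "scores (low versus high"), with an interaction test as the method.

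The section on baseline measures describes GREP as a tool covering attributions about enduring pain, sensitivity to pain and willingness to report it. It gives no score range or distribution. No analysis that uses the score as a continuous variable is stated anywhere. The significance level that applies is in Primary Analyses: "A two-sided significance level of .05 will be used for all inferential analyses". The Sample Size section covers the main effect only.

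**The concern.** The question is whether the treatment effect varies with the strength of a patient's gender-based pain expectations. If it varies gradually, a two-category moderator ignores all differences within each half and treats patients just either side of the cut as different in kind. The same interaction model could use the score as measured.

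Two features make the loss matter more than it otherwise would. An interaction test in a sample sized for a main effect starts with low power. The plan also uses the test as a gate: without a significant interaction, no group-specific effects are estimated. A less sensitive test therefore makes it more likely that a real gradient goes both undetected and undescribed.

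**Working it through.** **Inputs from the documents.** Sample Size: two-sided alpha .05, SD 20 on a 0-100 scale, 80% power for 10 points, 64 per group, 10% loss, 256 complete patients over both sites, design effect 1.5. Primary Analyses: two-sided .05 for every test.

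**Assumptions not in the documents.** The residual SD for the interaction is 20; moderation is linear in GREP; the split is at the median unless stated; the score is normal unless stated. The design effect of 1.5 is the plan's allowance for the combined main effect. It is carried over here only to show a less favourable case.

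**1. The plan's own figures reproduce.**
- Per group: 2 × (1.96 + 0.8416)² × 20² / 10² = 62.8, so 63 by the normal approximation. The t-test version gives 63.8, so 64, or 128 in total.
- Loss to follow-up: 64 / 0.90 = 71.1, so 72 per group and 144 in total.
- Combined sample: 2.8016 × 20 × √(2 / (128/1.5)) = 8.58 points (d = 0.43), which matches the stated 8.6.

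**2. How weak the high/low interaction test is.** With a share p in the high group, SE = 20 × √[(4/N) × (1/p + 1/(1−p))]. The detectable interaction at 80% power is 2.8016 × SE. With p = 0.5:

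| Sample | SE | Detectable interaction | Power for a 10-point interaction |
|---|---|---|---|
| 256, no design effect | 5.00 | 14.0 | 52% |
| 256, design effect 1.5 | 6.12 | 17.2 | 37% |
| One site, 128 | 7.07 | 19.8 | 29% |

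The planned main effect is 10 points.

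**3. Information lost by splitting.** Under linear moderation, the share kept is the squared correlation between the score and its high/low indicator. For a normal score cut at the median this is 2/π = 0.637, a loss of 36%. Other cuts of a normal score lose more: 38% at 40/60, 42% at 30/70 and 51% at 20/80. For a median split of other shapes, the loss is 25% (uniform), 25% (a bimodal example), 30% (beta(2,2)), and 48% to 52% (lognormal, Laplace and exponential examples). In the normal case, 256 split patients carry the information of 256 × 2/π = 163 analysed continuously. Matching 256 analysed continuously would take 256 × π/2 = 402.

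**4. What that does to power.** For the continuous score, SE = 2 × 20 / √256 = 2.5 points per GREP SD. With the design effect it is 2.5 × √1.5 = 3.06. Splitting multiplies the z value by √0.637 = 0.798.

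| Interaction per GREP SD | Design effect | Continuous: z, power | Median split: z, power |
|---|---|---|---|
| 7 points | none | 2.80, 80% | 2.23, 61% |
| 7 points | 1.5 | 2.29, 63% | 1.82, 45% |
| 5 points | none | 2.00, 52% | 1.60, 36% |
| 3 points | none | 1.20, 22% | 0.96, 16% |

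**5. Check by simulation.** A high-low contrast of 10 points corresponds to 10 / (2√(2/π)) = 6.27 points per SD. With 256 patients and no design effect, the formulas give 71% power continuous and 52% split. A simulation of 4,000 trials gave 68% and 49%. With 128 patients the formulas give 43% and 29%, and the simulation 40% and 27%. The gap between the two analyses is confirmed; the absolute values are slightly lower.

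**The case against.** Several objections are fair, and some of them stand.

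- **The loss is assumption-driven.** This stands. The documents say nothing on the shape of the GREP score, so 36% cannot be stated as a fact about this trial. It belongs to a normal score, linear moderation and a median split, and the range above should go with it.
- **The continuous model is not free of cost.** This also stands. A linear term imposes a shape. If the effect changes abruptly at the cut, the split loses nothing and can be the more powerful test. Spline interactions in 256 patients would be imprecise. The documents give no reason to expect a threshold, so the continuous score remains the better default.
- **The remedy does not make the test adequate.** Correct. With the design effect, even 7 points per SD gives only about 63% power. That is a large gradient: 14 points between patients one SD below and one SD above the mean, more than the 10-point minimally important difference. At 3 points per SD both analyses are weak.
- **The consequence is limited.** Correct. The moderator is measured at baseline and named in advance, and it is tested by a formal interaction. A split fixed in advance costs efficiency; it does not bias the comparison or inflate type I error.

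A reader might also infer that the cut-point has been left open, or will be picked after the data are seen. The documents do not support that. Nothing says that the cut will be data-driven, and a journal article may leave a subgroup cut-point to the full protocol or analysis plan, neither of which is shown. The power loss does not depend on that reading, since it arises with a prespecified cut too.

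**Conclusion.** The point holds as one of efficiency. The article itself, in the text and in Table 3, fixes a two-category moderator where a score is available, so this is a stated choice and not a detail left to another document.

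If moderation is graded, the choice costs roughly a quarter to a half of the information at a median split, with 36% for a normal score. In the worked case of 7 points per SD, that is a drop of nearly 20 percentage points in power, with or without the design effect. The size rests on linear moderation, a residual SD of 20 and an assumed score distribution; there is no loss if the true effect steps at the cut.

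Severity is low. Only one subgroup question is affected, and the primary conclusion does not change.

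**What to change.** In Subgroup Analyses and in Table 3, make allocation by GREP score, entered as a continuous covariate in the same model, the primary interaction test. Then:

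- Add one simple check for non-linearity, named in advance.
- Report the estimated treatment effect with its confidence interval at chosen percentiles of the score, for example the 25th, 50th and 75th.
- Keep the high/low groups for display or as a supportive analysis.
- Reword the condition for follow-on analyses so that it refers to the continuous test.

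The cost is a few lines of wording, with no extra patients or data. The one statistical price is less sensitivity to a true step at the cut, which the supportive high/low analysis would still show. The text should also acknowledge that the interaction test remains of limited power in either form.
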